#### Control group

The participants in the control group will attend a low-intensity exercise program and receive health education but without similar training benefits in lower extremity weight bearing, strength, or balance [14]. The low-intensity exercise program will consist of whole body stretches, controlling breathing, and relaxation. Health education will cover health-related topics, such as ankle sprain, prevention, and rehabilitation. The weekly schedule will be identical to that of the STCEP group, and each session will include 40 min exercise and 20 min health education. Every training session will be led and monitored by a professional exercise instructor who will carefully guide the exercise and correct inappropriate movements.

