### Criteria for discontinuing or modifying allocated interventions {11b}

Study patients will be allowed or asked to withdraw from the study if:
Participants decide to withdrawParticipants develop serious diseases, such as heart disease or strokeParticipants have an adverse reaction related to the STCEP programParticipants missed more than three training sessions in the 12-week program

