### Outcomes {12}

Demographic information, primary outcomes, and secondary outcomes will be collected. Demographic information will be collected at baseline (1–2 weeks before randomization) via a questionnaire. Primary and secondary outcomes will be measured at baseline, 4th, 8th, and 12th weeks of training. The schedule of study outcome assessments is outlined in Fig. 3.

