### Sample size {14}

The sample size is estimated on G* Power software (Germany) on the basis of a previous study [12], which reported that the CAIT score increased from 17.6 ± 2.1 cm to 28.4 ± 2.4 cm after 12 weeks of Tai Chi training. Under a significance level of 0.05, a statistical power of 0.80 in the two-tailed test, and a drop-out rate of 20% [24], the effect size and estimated required sample size of two groups are 0.57 [12] and 104, respectively.

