## Statistical methods

### Statistical methods for primary and secondary outcomes {20a}

Data will be analyzed with SPSS 20.0 (IBMS, NY, USA) and expressed as mean ± standard deviation. Two-way repeated ANOVA will be used to determine the main effects of groups, intervention time, and interaction on the measurements. If any significant main and interaction effects will be found, the Bonferroni method will be conducted for post hoc comparisons. The significant level will be set at 0.05.

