### Methods in analysis to handle protocol non-adherence and any statistical methods to handle missing data {20c}

If any participant withdraws from the trial, the last observation-carried forward method and multiple imputation method will be respectively conducted to adjust for the missing data.

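### LOCF and multiple imputation are both prescribed for the same missing data with neither named as primary, and LOCF shrinks the effect if the Tai Chi arm improves as the plan expects

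*Protocol article*

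**What the plan says.** Section {20c} of the protocol article is the only text on missing data. Its trigger is "If any participant withdraws from the trial", and its remedy is that "the last observation-carried forward method and multiple imputation method will be respectively conducted to adjust for the missing data". The word *respectively* has nothing to attach to: no outcome, visit, reason for withdrawal, or primary or supportive role is assigned to either method.

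The analysis that receives the filled data is in section {20a}: "Two-way repeated ANOVA will be used to determine the main effects of groups, intervention time, and interaction on the measurements". That section does not say which filled data set it uses.

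Three other places bear on the size of the problem:
- Outcomes {12}: "Primary and secondary outcomes will be measured at baseline, 4th, 8th, and 12th weeks of training".
- Sample size {14}: the cited study found that "the CAIT score increased from 17.6 ± 2.1 cm to 28.4 ± 2.4 cm after 12 weeks of Tai Chi training", and the calculation assumes "a drop-out rate of 20" per cent, with no split by arm.
- Section {11b}: one withdrawal reason, an adverse reaction to the Tai Chi program, can arise only in that arm. The others, including having "missed more than three training sessions in the 12-week program", apply to both.

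**The concern.** Two issues are joined here.

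First, LOCF and multiple imputation rest on different assumptions and will generally give different answers. With no role fixed in advance, the choice of headline result could be made after both are seen.

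Second, LOCF assumes that a participant's score stops moving at the last visit. The trial is built on the opposite expectation for the Tai Chi arm. Someone who leaves before week 4 would enter the week-12 comparison with zero change. LOCF is also a single imputation: filled values are analysed as if observed, so the standard errors carry no uncertainty from the filling.

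At stake are a diluted estimate of a real effect and, under further conditions, a difference between arms that comes only from who left and when.

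**Working it through.** The plan gives no figure for the effect of missing data, so there is none to reproduce. The planned total of 104 enters only as 52 per arm in the simulation.

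**Inputs from the document**
- Visits at weeks 0, 4, 8 and 12 (Outcomes {12}).
- Tai Chi gain on CAIT: 28.4 − 17.6 = 10.8 points (Sample size {14}).
- Effect size 0.57 and overall loss 20% (Sample size {14}).

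**Assumptions**
- Change is linear over the four visits, drop-outs' last visits are spread evenly over baseline, week 4 and week 8, and loss is unrelated to outcome.
- Control gain is not given; a range of 0 to 8 CAIT points is shown.
- Loss by arm is not given; 20/20, 30/10 and 10/30 (STCEP/control, %) are shown.

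**Formula.** Under LOCF a drop-out keeps on average (0 + 1/3 + 2/3)/3 = 1/3 of the 12-week gain. With loss d, an arm's mean gain is multiplied by m(d) = (1 − d) + d/3 = 1 − 2d/3. So m(0.1) = 0.933, m(0.2) = 0.867 and m(0.3) = 0.800. The LOCF difference is m(d_T)·g_T − m(d_C)·g_C.

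**Step 1: equal loss.** At 20/20 both gains carry the same factor, so the difference is multiplied by 0.867 (−13.3%) whatever the control arm does. On CAIT with a flat control arm, 10.8 × 0.867 = 9.36. On the standardised effect, 0.57 × 0.867 = 0.49.

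**Step 2: range over control gain and loss split (CAIT points, Tai Chi gain 10.8)**

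| Control gain | True difference | 20/20 | 30/10 | 10/30 |
|---|---|---|---|---|
| 0 | 10.8 | 9.36 (−13.3%) | 8.64 (−20.0%) | 10.08 (−6.7%) |
| 2 | 8.8 | 7.63 (−13.3%) | 6.77 (−23.0%) | 8.48 (−3.6%) |
| 5 | 5.8 | 5.03 (−13.3%) | 3.97 (−31.5%) | 6.08 (+4.8%) |
| 8 | 2.8 | 2.43 (−13.3%) | 1.17 (−58.1%) | 3.68 (+31.4%) |

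With a flat control arm every entry is a shrinkage. Inflation appears only where the control arm gains enough and loses more participants.

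**Step 3: no true effect.** If both arms gain g, the bias is g × (2/3)(d_C − d_T). For an assumed g of 0.9 SD and 10% versus 30% loss, 0.9 × 0.133 = 0.12 SD, positive if control loses more and negative if STCEP does. It is zero if loss is equal or if neither arm changes. In CAIT points it is ±0.27 for g = 2 and ±0.67 for g = 5.

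**Step 4: true effect 0.57 SD on the same 0.9 SD trend** (STCEP gain 1.47 SD). At 30/10: 1.47 × 0.800 − 0.9 × 0.933 = 0.34. At 10/30: 1.47 × 0.933 − 0.9 × 0.800 = 0.65.

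**Step 5: simulation** (52 per arm, 5,000 runs, assumed within-person correlation 0.5, t-test on change to week 12). With gains of 10.8 and 5 (true difference 5.8), LOCF averaged 5.03, 3.96 and 6.07 at 20/20, 30/10 and 10/30, in line with Step 2. The observed week-12 data averaged 5.79 to 5.81. With both arms gaining 5 points and no true difference, LOCF's type I error was 0.052 at 20/20, 0.253 at 30/10 and 0.260 at 10/30; the observed data stayed between 0.048 and 0.055.

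These figures concern the week-12 contrast and not the full repeated-measures ANOVA. Non-linear gains and the CAIT maximum of 30 would alter their size.

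**The case against.** **The control arm may not change.** No section says that it will. The comparator is described as one where participants "receive health education but without similar training benefits in lower extremity weight bearing, strength, or balance". A reader might infer that both arms move and that LOCF will therefore manufacture a difference. The document does not support that. With a flat control arm, LOCF can only shrink the Tai Chi effect under the assumptions used here. This objection stands.

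**Unequal loss is not forecast.** Only an overall 20% is given. One withdrawal reason is specific to STCEP, the others are common to both arms, and the protocol calls the intervention low risk. Unequal loss is possible, but 30/10 is an illustration. This also stands.

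**The 0.9 SD trend is not the plan's.** It is far smaller than the cited Tai Chi gain, which is 10.8 points on SDs of 2.1 and 2.4, more than 4 SD. The false-positive risk depends heavily on this input. A 0.12 SD shift against a standard error of √(2/52) = 0.196 SD gives a two-sided error of roughly 9% by normal approximation, while the 25% in Step 5 needs a 5-point gain in both arms. Neither should be quoted as the trial's error rate.

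**LOCF is not always biased when data are missing completely at random.** With equal loss and no true effect the bias is zero and the simulated type I error is 0.052. The neglect of imputation uncertainty did not show there as an inflated error rate.

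**Roles may be set in an unseen analysis plan.** The wording could mean that each method is run separately so the results can be compared, and running both would expose a discrepancy. That softens the lack of a primary method. It does not rescue LOCF, which the article itself prescribes on equal terms with multiple imputation.

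**Conclusion.** The point holds in a limited form. Section {20c} fixes two methods for the same missing data and does not say which gives the trial's result; that needs no assumption. LOCF is a poor choice on the plan's own expectation of improvement in the Tai Chi arm: about 13% shrinkage of a true effect at 20% loss in each arm, given linear change, evenly spread last visits and loss unrelated to outcome. This shrinkage needs neither control-arm change nor unequal loss.

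Bias in either direction, or a spurious difference under no true effect, is conditional on control-arm improvement together with unequal loss. The document makes unequal loss possible and forecasts neither condition, so ±0.12 SD is an illustration. Confidence is high on the wording and on the direction of the shrinkage, and lower on any size beyond the equal-loss case. The point should be corrected before analysis; it does not undermine the design.

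**What to change.** Name one primary approach that is valid under missing at random. Either of these would do:
- the multiple imputation already listed, done by arm and using baseline and earlier visits; or
- a likelihood-based mixed model on all observed visits of all randomised participants, which needs no imputation step.

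Then delete LOCF or label it supportive only, and state in section {20a} which data the primary analysis uses. The first option is the smaller change, because multiple imputation is already in the plan. A delta-adjusted or control-based sensitivity analysis for departures from missing at random would be a useful but optional addition.

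The cost is wording and a little programming; no new data are needed.

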### Plans to give access to the full protocol, participant-level data, and statistical code {31c}

The datasets analyzed during the current study are available from the corresponding author upon reasonable request.

## Oversight and monitoring

### Composition of the coordinating center and trial steering committee {5d}

The group of the coordinating center will be composed of teachers in the College of Sports and Health, Shandong Sport University. The trial steering committee will consist of three main investigators in this study, the administrative staff of funding and process supervision.

### Composition of the data monitoring committee, its role, and reporting structure {21a}

Making plans to consider a data monitoring committee is unnecessary because this intervention is a low risk.

### Adverse event reporting and harms {22}

The trial will not use investigational medicinal products, and the researchers have already obtained the practicing certificate of a rehabilitation therapist with abundant clinical experience. The participant will be monitored and documented during the study intervention. Any adverse events (defined as any functional impairment caused by the intervention, such as ankle sprain, ankle pain, and pallor) will be recorded. If serious adverse events occur, the participants will immediately discontinue the intervention and receive appropriate treatments. Incidents will be reported to the Ethics Committee of Shandong Sport University.

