## Introduction

### Background and rationale {6a}

Acute ankle sprain is one of the most common musculoskeletal injuries in sports [1]. Approximately 40–75% of ankle sprains may lead to chronic ankle instability (CAI) [2]. Functional ankle instability (FAI) is the most common type of CAI. The symptoms of FAI include giving away or subjective ankle instability, sensorimotor impairments, and a high ankle sprain recurrence rate [3]. Individuals with FAI have a substantially higher risk of ankle abnormal biomechanics, which may lead to ankle osteoarthritis. This condition will adversely affect the daily living activities of patients with FAI [2].

Neuromuscular control at the ankle provides the unconscious activation of dynamic restraints that occur in preparation for and in response to ankle joint motion and loading [4]. Repeated ankle sprains may lead to neuromuscular deficits, which significantly impair the ankle stability [5]. Patients with FAI have deficits on joint position sense on the affected side compared with those of the healthy contralateral side [6]. Caulfield et al. collected the surface electromyography (sEMG) of peroneus longus of patients with FAI during landing tasks. They found that activation in the peroneus longus muscle reduces during the experimental period immediately prior to initial contact compared with that of the healthy control [7]. In addition, Delahunt et al. found that patients with FAI have a reduced dorsiflexion position and a decreased sagittal plane angular velocity during landing compared with those of the healthy control [8]. Therefore, the neuromuscular function of patients with FAI should be improved to prevent and treat ankle sprain injury.

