**Fig. 2 Fig2:**
[figure not shown]
The core program consisting of nine forms of STCEP

Form A: part the wild horse’s mane (stepping diagonally forward: left and right)

Form B: step back up and whirl arms (stepping backward: left and right)

Form C: brush knee and twist step (stepping forward: left and right)

Form D: cloud hands. Form E: single whip (stepping sideways: left and right)

Form F: pushing down and single on one leg (stepping diagonally forward: left and right)

Form G: heel kick (in situ: left and right)

Form H: grasp the bird’s tail (stepping sideways: left and right)

Form I: cross-hand (stepping sideways: left and right)

The exercise routine emphasizes the practice of ankle joint movements with more repetitions in multiple directions, which may help improve the neuromuscular function of ankle joints in patients with FAI. These movements are usually maintained in a semi-squat and one-leg stance, controlling the displacement of the center of gravity in three anatomical planes. The coordination of all body parts plays a vital role in maintaining precise motor control while keeping balance. Any simple action in the traditional 24-style Tai Chi program that involves fewer foot-ankle movements is removed. Afterward, the rest of the movements are rearranged according to the suggestions of Tai Chi experts. The exercise program will be specially designed to promote the neuromuscular control of patients with FAI.

The participants in the STCEP group will receive 12 weeks of the STCEP training, three sessions per week, and 60 min per session. Each session will include 5 min warm-up exercises, 50 min practice, and 5 min cool-down exercises. Every training session will be led and monitored by a professional Tai Chi instructor, who will carefully guide the exercise and correct inappropriate movements.

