### Strategies to improve adherence to interventions {11c}

The subjects’ attendance in every session will be recorded by the research assistant (who does not participate in follow-up evaluation and data analysis). The detailed exercise content and benefits will be informed to the participants to promote participant retention. The patients will be contacted and encouraged through WeChat three times a week. They will be asked about the factors that hinder their activities and solve them in time. In addition, teaching videos will be provided according to the teaching process to promote their exercise enthusiasm.

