## Discussion

This study will focus on the effect of STCRP on the neuromuscular function of individuals with FAI. Examining neuromuscular activities during the performance of a dynamic task can provide further insights into neuromuscular strategies utilized by individuals with FAI to maintain postural stability.

Tai Chi movements are performed with frequent body weight shifts between both legs and characterized by a low impact and a low loading rate [24]. Therefore, the activation of the muscles around the ankle may be increased during practicing. Tai Chi is performed with ankle flexion and extension in various directions, which may increase stimulations to the proprioceptors of the ankle joint. Wang et al. reported that adequate and appropriate mechanical loading is necessary to maintain physiological joint homeostasis [24].

We propose that Tai Chi exercise can be an effective exercise intervention as an option for individuals with FAI. However, the biomechanical mechanism and efficacy of Tai Chi in the treatment of FAI remain unclear. In this experiment, a rigorous random parallel control design will be conducted to observe the effectiveness and investigate the biomechanical mechanism of Tai Chi training on patients with FAI. This trial will provide new data and insights into the effectiveness of TC exercise and its influence on the clinical and functional aspects of FAI.

However, few limitations exist in this study. First, our sample size is small. Our recruitment strategy for this study (only in school) may have introduced some selection bias. Second, the participants and the instructors in this trial cannot be blinded. Their subjective expectations may skew the results.

In conclusion, this study attempts to estimate the effect of Tai Chi intervention on the neuromuscular function of individuals with FAI. It may provide evidence to support the beneficial effects of a Tai Chi exercise program on the neuromuscular function of individuals with FAI. The findings of this study will fill the research gap in the efficacy of Tai Chi based on the results of the proposed project. Further comprehensive research on the exercise rehabilitation of FAI will be proposed. Furthermore, the possible mechanism of Tai Chi on the neuromuscular function of patients with FAI may be discussed.

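### Adverse events are recorded only if attributed to the intervention, so all-cause sprains are not captured and any comparison of harms between arms depends on attribution

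*Protocol article*

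**What the plan says.** The harms section {22} sets the rule: "Any adverse events (defined as any functional impairment caused by the intervention, such as ankle sprain, ankle pain, and pallor) will be recorded". The sentence before it reads "The participant will be monitored and documented during the study intervention". The section does not say who decides whether the intervention caused an event.

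Other sections bear on how this rule works in practice:

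- The Background {6a} lists "a high ankle sprain recurrence rate" among the features of the condition. The inclusion criteria require at least two giving-way episodes in the previous 6 months.
- The Discussion concedes that "the participants and the instructors in this trial cannot be blinded". Section {17a} blinds outcome assessors, data managers and analysts.
- On the comparator, "The participants in the control group will attend a low-intensity exercise program and receive health education", and "The weekly schedule will be identical to that of the STCEP group". Both programmes are led by an instructor.
- The adherence section {11c} adds contact outside the sessions: "The patients will be contacted and encouraged through WeChat three times a week".
- The outcomes section {12} includes a single-leg landing from a 40-cm box and a timed leap test, at baseline and weeks 4, 8 and 12. It lists no count of sprains or giving-way episodes.

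**The concern.** In people whose ankles sprain repeatedly, some sprains will occur in both arms whatever the programmes do. For a single sprain it is hard to say whether training or the existing instability was responsible. Randomisation answers that question for the group, because a difference in all-cause counts between arms is the effect of assignment. A definition that requires the cause to be settled first discards the events needed for that comparison.

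At stake is what the trial can say about safety. Section {30} anticipates no harm, and section {21a} dispenses with a data monitoring committee because the intervention is considered low risk. Counts filtered by attribution could neither confirm nor challenge that view with confidence.

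**Working it through.** The plan states no figure on this point, so there is none to reproduce. The check has two parts: what the rule admits, and what attribution can do to a count by arm.

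**What the rule admits (events after randomisation)**

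| Event | Within the definition? | Counted by a listed outcome? |
|---|---|---|
| Sprain judged due to either arm's programme | Yes | No |
| Sprain in a session, judged due to existing instability | No | No |
| Sprain in daily life or sport, judged unrelated | No | No |
| Sprain in the landing or leap test at week 4, 8 or 12 | No, read literally: testing is not the intervention | No |

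Only the first row is sure to be recorded.

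**Could attribution differ between arms?** The person attributing is unspecified, and those closest to the events know the assignment. The programmes also differ in how plausible a cause they seem. The Tai Chi forms use semi-squat and one-leg stances, while the control programme is stretching, breathing and relaxation plus education. The discontinuation criteria {11b} name adverse reactions to the Tai Chi programme only. Different attribution is therefore plausible, but its size cannot be read from the documents.

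**What it does to a count**

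Inputs: n = 104 / 2 = 52 per arm (abstract, 1:1 allocation). The true 12-week sprain risk p and the probability a that a sprain is judged caused by the intervention are assumptions.

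- Expected recorded events per arm = n × p × a
- Recorded risk ratio = (true risk ratio) × (a in Tai Chi / a in control)

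With equal true risk in both arms, and a = 0.8 in Tai Chi and 0.2 in control:

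| True risk, both arms | True sprains per arm | Recorded, Tai Chi | Recorded, control | Recorded ratio |
|---|---|---|---|---|
| 10% | 52 × 0.10 = 5.2 | 5.2 × 0.8 = 4.2 | 5.2 × 0.2 = 1.0 | 4.0 |
| 20% | 52 × 0.20 = 10.4 | 10.4 × 0.8 = 8.3 | 10.4 × 0.2 = 2.1 | 4.0 |
| 30% | 52 × 0.30 = 15.6 | 15.6 × 0.8 = 12.5 | 15.6 × 0.2 = 3.1 | 4.0 |

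Other attribution pairs under equal true risk:

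- 0.8 and 0.5 give a recorded ratio of 0.8 / 0.5 = 1.6.
- 0.5 and 0.1 give 0.5 / 0.1 = 5.0.
- 0.5 and 0.5 give 1.0, but half the sprains are lost.

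In the other direction, take true risks of 20% (Tai Chi) and 10% (control), with attribution of 0.3 and 0.6. The recorded risks are 0.20 × 0.3 = 6% and 0.10 × 0.6 = 6%, so a true doubling disappears.

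The rule can thus create a difference, hide one, or leave the ratio intact while losing events.

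**The case against.** The strongest reply has five parts.

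- **The article condenses a fuller protocol.** Event forms, elicitation questions and the person judging relatedness are commonly left to that document. This stands, so their absence is not the complaint. The definition is stated in the article, and it is the definition that excludes events.
- **Nothing confines recording to training sessions.** A reader might infer that it does, from the sentence on monitoring. The text does not support this: the Trial design section {8} applies the word intervention to the whole 12 weeks, which is the more natural reading here too. What remains is that the window should be stated outright.
- **The article does not say that an unblinded person attributes events.** Correct: it names nobody. Participants and instructors are unblinded, but data managers and assessors are not. The supportable statement is that the person attributing is unspecified.
- **Sprain recurrence is neither an objective nor an outcome, and no comparison of adverse events is announced.** True, and it limits the severity. The article nevertheless promises to record adverse events and names sprain as its first example. Whoever reads the results will compare the arms.
- **The Cumberland Ankle Instability Tool collects instability and ankle pain in both arms at four time points, whatever the cause.** This is partial cover. It is a score at scheduled visits and does not count sprains.

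The control arm also receives a supervised programme, so attributed events could occur and be tabulated there. That stands as well. Such a table can be made, but it depends on attribution.

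**Conclusion.** The point holds as a fault in a stated rule. Recording depends on a causal judgement by an unspecified person, in a trial with unblinded participants and instructors. Sprains and ankle pain not attributed to a programme, including those arising in the trial's tests, are outside the rule. All-cause events are not captured, and a comparison of harms by arm cannot be separated from attribution.

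A reader might go further and infer that harm from the Tai Chi programme will be under-counted. The documents do not support that. Events judged to come from the programme are the ones the definition keeps, and the recorded ratio can move either way. What is certain is that unattributed events are lost.

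The numerical size is illustrative, because every risk and attribution rate used is assumed. The conclusion about the definition does not depend on them. The efficacy analyses are not affected. This is a change that should be made to protect the safety reporting.

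**What to change.** In section {22}:

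1. Define an adverse event as any untoward event from randomisation to week 12 in both arms, whatever the suspected cause and wherever it occurs, assessments included. Name any ankle sprain and any new or worse ankle pain explicitly.
2. Record relatedness as a separate field, completed after the event has been logged.
3. Ask the same neutral question in both arms at existing sessions or WeChat contacts.
4. Report all events by assigned arm, with relatedness shown alongside.
5. State that the monitoring period is the full 12 weeks.

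Baseline testing precedes randomisation, so an injury there belongs to no arm and lies outside this window.

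The change to the text is small. The cost is a longer list of mostly minor events and some added recording work. Asked once a week, the question is put up to 104 × 12 = 1,248 times; asked at all three weekly contacts, up to 104 × 12 × 3 = 3,744 times. Weekly asking is the lighter option.

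The Trial status section says recruitment began on 22 September 2021. The report should therefore give the date of the change and mark events collected under the narrower definition.

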## Assignment of interventions: allocation

### Sequence generation {16a}

After the baseline assessment, the participants will be randomly assigned to the STCEP group and the control group at a ratio of 1:1. SPSS version 22.0 (IBM, NY, USA) will be used for random allocation. A randomization sequence will be created by an independent research assistant.

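### Withdrawal and harms sections set unreconciled rules for the same ankle events, and the reaction-based withdrawal ground exists only for the Tai Chi arm

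*Protocol article*

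**What the plan says.** Two sections of the protocol article deal with a participant who has an adverse event.

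- **Adverse event reporting and harms {22}.** "Any adverse events (defined as any functional impairment caused by the intervention, such as ankle sprain, ankle pain, and pallor) will be recorded". The next rule concerns serious events: "If serious adverse events occur, the participants will immediately discontinue the intervention and receive appropriate treatments". What stops is the intervention; leaving the study is not mentioned.
- **Criteria for discontinuing or modifying allocated interventions {11b}.** The list opens "Study patients will be allowed or asked to withdraw from the study if" and gives four grounds: the participant's own decision, serious disease, an adverse reaction related to the Tai Chi programme (STCEP), and more than three missed sessions. The reaction ground has no severity qualifier and names only STCEP.

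Neither section refers to the other or says which governs.

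Two further sections decide what follows. The missing-data section {20c} states: "If any participant withdraws from the trial, the last observation-carried forward method and multiple imputation method will be respectively conducted". Under Outcomes {12}, the CAIT is a primary outcome made up of eight instability items and one ankle pain item, measured at baseline and at weeks 4, 8 and 12.

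**The concern.** The harms section defines an adverse event by its cause: "defined as any functional impairment caused by the intervention, such as ankle sprain, ankle pain, and pallor". In the Tai Chi arm the intervention is STCEP, so every recorded event also meets the reaction ground in {11b}. The two sections therefore cover the same events but differ in two respects:

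- the trigger: any STCEP-related reaction, or a serious event only;
- the consequence: leaving the study, or stopping the intervention.

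The choice affects who is measured at week 12. The events named are ankle events, the population has unstable ankles, and the CAIT asks about instability and pain. Withdrawal for ankle pain is therefore likely to be related to the outcome. Because the ground names one programme only, it can remove symptomatic participants from one arm without a matching rule in the other. That would undermine the comparison that randomisation sets up.

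**Working it through.** **1. The sections side by side, for a non-serious STCEP-related event such as ankle pain.**

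| | Withdrawal criteria {11b} | Harms {22} |
|---|---|---|
| Does the event qualify? | Yes, any related reaction | Yes, as an adverse event |
| Stated action | Allowed or asked to withdraw | Recorded |
| What ends | Study participation | Nothing stated |
| Same event caused by the control programme | Not listed as a reaction ground | Recorded |

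For a serious STCEP-related event, {11b} applies in the same way and {22} adds immediate stopping of the intervention.

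**2. Can both be obeyed?** Yes. An event can be recorded and the participant can also be allowed or asked to withdraw. The difficulty is that recording alone, permitting withdrawal and requesting withdrawal are all compatible with the text. Participants may already leave at any time under the consent provisions {26b} and the first ground in {11b}. What the reaction ground adds is mainly that staff may ask them to go, and nothing says when they should.

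**3. What happens to the data.** With visits at weeks 4, 8 and 12, someone who leaves after an event in week 6 has a last value from week 4, before the event. Last observation carried forward reuses that value. Multiple imputation that uses only observed scores would draw mainly on participants who stayed. If *p* is the share of the Tai Chi arm withdrawn on this ground and *δ* is the mean difference between the filled-in value and the value that would have been observed, the arm mean shifts by *p* × *δ*. For each CAIT point of *δ*, the shift is 0.1, 0.2 or 0.3 points at *p* = 10%, 20% or 30%. The sign of *δ* is not known. An early value understates later improvement, but it also conceals a deterioration that came with the event.

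**4. Power, as an illustration only.** The protocol states that "the effect size and estimated required sample size of two groups are 0.57 [12] and 104, respectively", with 1:1 allocation, so 104 / 2 = 52 per arm. The documents give no event rate; 10%, 20% and 30% are assumptions. The calculation takes the extreme case: everyone affected leaves, only completers are analysed, and there is no other loss. It uses a two-sample t test, two-sided 0.05, d = 0.57.

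| Assumed rate | Leaving (of 52) | Analysed, Tai Chi v control | Power |
|---|---|---|---|
| 0% | 0 | 52 v 52 | 0.821 |
| 10% | 5.2, about 5 | 47 v 52 | 0.801 |
| 20% | 10.4, about 10 | 42 v 52 | 0.776 |
| 30% | 15.6, about 16 | 36 v 52 | 0.739 |

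If both arms have already lost the stated 20% (41.6 per arm), power is 0.729. A further loss of 10% or 20% of the remaining Tai Chi participants takes it to 0.705 or 0.677.

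The stated total of 104 is an input here and is not reproduced. The same test needs 50 per arm, 100 in total, and 100 / 0.8 = 125 with 20% drop-out. That is a separate matter and does not bear on this point.

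**The case against.** The strongest case against is that the sections form a graded scheme: record everything, allow or ask withdrawal after a related reaction, and stop training at once when the event is serious. Much of this stands, and it rules out several stronger readings that a reader might infer.

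- *Non-serious events are to be recorded and nothing more.* The harms section says they are recorded. It does not exclude withdrawal or require training to continue.
- *Staff cannot comply with both sections.* They can, because allowing or asking is not compulsion.
- *A mild case leaves follow-up while a serious one stays.* A serious STCEP-related event also meets the {11b} ground, so the text does not produce this reversal.
- *A fixed number leave under one section and none under the other.* This treats permission as compulsion in one place and silence as prohibition in the other, on assumed rates.

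It is also fair to say that the heading of {11b} concerns interventions, so withdrawal from the study may be loose wording for leaving the programme. Control participants can leave on the other three grounds. The plan imputes for withdrawals and asks for consent to use their data. Even 16 of 104 is 15.4%, below the stated 20% drop-out.

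Three things survive. If the wording in {11b} is loose, that is itself a reason to correct it, because a reader following it literally ends follow-up. Imputation does not restore outcomes that were never measured, and consent to use existing data does not create later visits. Finally, this is not detail that an article leaves to a fuller protocol: two rules are stated, with different triggers and consequences, and one of them names a single arm.

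**Conclusion.** The concern holds as an unreconciled ambiguity with a one-sided consequence, not as a contradiction. Followed as written, {11b} permits outcome-related withdrawal from the study on a ground that exists only for the Tai Chi arm, while {22} ties stopping to serious events and to the intervention alone. The same non-serious ankle event can be handled differently by different staff without breach of either section.

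The size cannot be determined: the documents give no event rate and do not say how often staff would ask a participant to leave. Under the assumed rates and the completers-only extreme, the power loss is small to moderate (0.82 to between 0.80 and 0.74). Selective loss in one arm matters more, and its direction is not known. The conclusion rests on the literal wording of the two sections and on ankle symptoms being related to CAIT scores, which the content of the instrument supports. No view is taken on which clinical rule is right.

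**What to change.** Reconcile {11b} and {22} into one rule, stated identically in both sections. It should:

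- refer to a reaction to the allocated programme, so that the same words apply to both arms;
- state separately, for each class of event, whether it ends training and whether it ends outcome follow-up;
- say whether withdrawal is offered or requested, so that staff do not have to choose.

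The clinical threshold for each class is for the sponsor's clinicians to set. The trial report should give the number and reasons for stopping training and for leaving follow-up, separately and by arm.

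The cost is a wording amendment and a note to instructors and assessors. Anyone who stops training but stays in follow-up would attend visits already scheduled, so no visits are added. Because recruitment has begun, the amendment should be dated, and any withdrawals already made on the reaction ground should be identified.
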